### Postintervention Procedure

At the completion of the intervention, the participant’s weight (kg) will be recorded. An HbA_1c_ test will be performed by the research teams’ CDE (DI). The online Australian diabetes-specific QoL questionnaire will be readministered. An online patient global impression of change questionnaire will be administered to determine the participants’ perception of the degree of change following the intervention relating to glycemic control and QoL [70]. This questionnaire will consist of 2 questions using a 7-point scale (“no change/has got worse” to “a great deal better/considerable improvement”). Finally, in an individual interview, each participant will be asked 5 questions regarding the CGMS experience relating to its acceptability, perception, benefits, and barriers. An interview question guide will be used to facilitate the interview. Data will be transcribed, coded, and parsed for common themes for inclusion in a publication.

### Potential Adverse Events

Potential adverse events may include hypoglycemia, hyperglycemia, blood ketones, and diabetic ketoacidosis episodes. Any adverse events will be discussed by PD and the participant, and a plan will be put in place to prevent any future occurrences. However, adverse events are not expected to occur due to the safety alerts thresholds that will be set up on the CGM as recommended by the CGM use guidelines [71].

### Outcomes

The primary outcomes will be divided according to the study phases. Primary outcome 1 will be related to the development and piloting of the new Australian diabetes-specific QoL questionnaire in study phase 1. Primary outcome 2 will be related to the validation of the study-developed questionnaire in study phase 2. Study phase 3 will produce 3 subdeliverables that will examine the association between a low carbohydrate diet and glycemic control in adults with T1DM (primary outcome 3.1), examine the association between a low carbohydrate diet and QoL in adults with T1DM (primary outcome 3.2), and investigate whether a low carbohydrate diet mediates the relationship between QoL and glycemic control in adults with T1DM (primary outcome 3.3).

This study will have no secondary study outcomes.

Figure 1 schematically shows the relationship between the study objectives. The association between QoL, low carbohydrate diet, and glycemic control variables have been represented with double-headed arrows. This indicates that the direction of the association is unclear and may be bidirectional in nature, as each variable has the potential to influence the other [13,19,30].

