### Intervention Procedure

All participants will follow a prescribed meal plan to meet their estimated energy needs as per the Schofield formula [64]. Meal plan macronutrient distribution will be 20% carbohydrate, 25% protein, and 55% fat based on the Australian book, *The CSIRO Low Carb Diet* [65]. The meal plan contains no more than 100 g per day of dietary carbohydrate, making this intervention a low carbohydrate dietary regimen according to Feinman et al’s [16] 2015 definition. Alcohol influences blood glucose levels, food and fluid choices, and quantities consumed [66]. For this reason, participants will be strongly advised to abstain from alcohol consumption during the 12-week intervention. Weekly telephone follow-up will be conducted by JP to discuss any concerns or questions participants may have. Follow-up by telephone has been shown to be an effective method to monitor medical nutrition therapy [67,68]. Weekly telephone appointments will also be conducted by the research teams’ endocrinologist (PD) to discuss blood glucose level management and adjust insulin doses as needed.

Any hypoglycemia treatment will be recorded in the food diary and will detail when, what, and how much carbohydrate was used to treat the hypoglycemic event. If any hypoglycemic events occur, PD will discuss this with the participant during the weekly telephone appointment and advice will be provided to avoid future occurrences. Participants will check blood ketones once a week on the morning after an overnight fast to avoid diabetic ketoacidosis. If blood ketones are present (>0.6 mmol/l), participants will follow a “sick day” management plan, and, if unsure what to do, will contact PD for advice. Participants will be encouraged to follow their usual exercise habits, as no exercise advice will be given [69]. This study is unique, and if a participant feels they are unable to complete the 12-week intervention, they may withdraw at any time.

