### Statistical Plan

Table 4 outlines a brief summary of the study objectives, the independent and dependent variables relating to each objective, and the planned statistical analyses to be conducted.

**Table 4 table4:** Brief statistical plan.

Statistical objectives	Independent variable	Dependent variable	Statistical analysis
To develop and pilot the Australian diabetes-specific quality of life questionnaire	Australian diabetes-specific quality of life questionnaire	N/A^a^	Transcribe, code, and identify common themes in the interview data
To validate the Australian diabetes-specific quality of life questionnaire (study developed)	Australian diabetes-specific quality of life questionnaire	Factorial validation indicators: root mean square error of approximation, comparative fit index, and Tucker-Lewis index	Exploratory factor analysis, confirmatory factor analysis, and structural equation modelling
To examine the association between a low carbohydrate diet and glycemic control	Low carbohydrate diet	Glycemic control	Bivariate: ANOVA^b^ and correlations. Multivariate: hierarchical regression controlling for sociodemographic covariates.
To examine the association between quality of life and a low carbohydrate diet	Low carbohydrate diet	Quality of life	Bivariate: ANOVA and correlations. Multivariate: hierarchical regression controlling for sociodemographic covariates.
To investigate whether a low carbohydrate diet mediates the relationship between quality of life and glycemic control	Low carbohydrate diet	Glycemic control and quality of life	Bivariate: ANOVA and correlations. Multivariate: hierarchical regression controlling for sociodemographic covariates.

^a^N/A: not applicable

^b^ANOVA: analysis of variance

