## Discussion

This study is the first of its kind to examine the association between a low carbohydrate diet, QoL, and glycemic control. This cross-sectional study protocol aims to develop, pilot, and validate a diabetes-specific QoL questionnaire and determine if an association exists between QoL and glycemic control while using a low carbohydrate dietary intervention in Australian adults living with T1DM.

The strengths of this study are that, to our knowledge, no previous published research has evaluated a low carbohydrate diet and its influence on QoL and glycemic control in Australian adults living with T1DM. Moreover, this is the first study to develop and validate an Australian T1DM-specific QoL questionnaire Therefore, the strengths of this study are its unique approach.

The potential limitations of this study include the fact that, first, the Australian diabetes-specific QoL questionnaire is not available to those who are vision impaired, intellectually impaired, or have any other type of diabetes, such as T2DM and gestational diabetes mellitus. Future studies could develop resources to include these populations. Second, in study phases 1 and 2, questionnaire data will be self-reported and may have the potential to produce social desirability bias [73]. However, using self-reported data is the most feasible option for this pilot study in order for the sample size (N=364) and statistical validation of the questionnaire to be achieved. Third, study phase 3 has been designed as a nonrandomized intervention group pilot study that will inform the design and feasibility of a potential larger randomized control trial. Finally, in study phase 3, there is potential selection bias: individuals who are highly motivated to improve glycemic control are more likely to participate [25].

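### Primary outcome 3.3 casts the prescribed diet as a mediator, a role it cannot fill when every participant is assigned it, and the variable roles in Table 4 contradict the objective

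*Protocol article*

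**What the plan says.** The Outcomes section lists three primary outcomes for phase 3. The third, 3.3, is to "investigate whether a low carbohydrate diet mediates the relationship between QoL and glycemic control in adults with T1DM". The same section says there are no secondary outcomes. Of the double-headed arrows in Figure 1 it says: "This indicates that the direction of the association is unclear and may be bidirectional in nature".

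The last row of Table 4 (Statistical Plan) repeats the objective: "To investigate whether a low carbohydrate diet mediates the relationship between quality of life and glycemic control". It enters the low carbohydrate diet as the independent variable and "Glycemic control and quality of life" as the dependent variable. The analyses are "Bivariate: ANOVA and correlations" and "Multivariate: hierarchical regression controlling for sociodemographic covariates". The rows for 3.1 and 3.2 carry the same analysis text.

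On who receives the diet, the Intervention Procedure section states: "All participants will follow a prescribed meal plan to meet their estimated energy needs as per the Schofield formula". One macronutrient distribution applies to all. The Discussion says that "study phase 3 has been designed as a nonrandomized intervention group pilot study", and no comparison group is described.

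The Preintervention Procedure section asks each participant for a daily food diary in the week before the intervention and throughout its 12 weeks, and says the records will enter the final analysis. It does not say in what role.

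**The concern.** A mediator sits on the path between an exposure and an outcome: the exposure changes it, and it changes the outcome. Objective 3.3 therefore implies the path QoL → diet → HbA1c. A diet that the study prescribes to every participant is set by the protocol and not by anyone's QoL, so the first arrow is missing for the assigned diet. The one place that gives variable roles, Table 4, then describes a different structure, diet → QoL and diet → HbA1c, in which nothing is a mediator.

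At stake is one of the three phase 3 primary outcomes. If the Table 4 analyses were run and reported under the objective as worded, readers would be told that a causal pathway had been tested when it had not. The article hopes that the intervention results will inform clinicians and could support a dietary guideline, so the wording of this claim matters.

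**Working it through.** **The plan's own figure.** The article gives no number for 3.3. Its only phase 3 calculation (Sample Size) is 16 completers to detect a 1.0% HbA1c difference at significance level 0.05 and power 0.8. No SD is stated, so it cannot be reproduced; a two-sided paired t test returns 16 if the SD of change is about 1.33%. Nothing below rests on that calculation.

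**Step 1: the assigned diet as mediator M.** Let X = QoL and Y = HbA1c. The two regressions are

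- M = i₁ + aX + e₁
- Y = i₂ + c′X + bM + e₂

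and the indirect effect is a·b. If every participant is assigned the diet, M = 1 for all. Then Var(M) = 0 and a = 0. In the second regression the columns are the intercept (all 1), X, and M (all 1). Two columns coincide, the matrix has rank 2 of 3, and b cannot be estimated.

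**Step 2: before/after coding.** Set M = 0 before and M = 1 after the intervention. Each person contributes one row of each, so the mean of M is 0.5. The covariance of baseline QoL with M is proportional to Σ(Xᵢ − X̄)(0 − 0.5) + Σ(Xᵢ − X̄)(1 − 0.5) = 0, so a = 0 by design. If QoL at each visit is used instead, its association with M is simply the mean change in QoL. That describes QoL changing over the intervention, not QoL influencing the diet.

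**Step 3: the roles side by side.**

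| | Exposure | Mediator | Outcome |
|---|---|---|---|
| Objective 3.3 | QoL | Diet | Glycemic control |
| Table 4, last row | Diet | none | Glycemic control and QoL |

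The regression in that row adjusts for sociodemographic covariates only. With the roles as listed, no fitted coefficient corresponds to a or b above. Structural equation modelling appears in Table 4 only for questionnaire validation.

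**Step 4: diary-measured intake as mediator (an illustration, not the plan).** Intake varies between people, so Steps 1 and 2 do not apply to it. The article gives no path sizes, so they are assumed: standardized, a = b, no direct effect. Success means both paths significant at 0.05 two-sided (4,000 simulated trials each).

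| a = b | Power, n=16 | Power, n=23 |
|---|---|---|
| 0.3 | 3% | 7% |
| 0.5 | 20% | 40% |
| 0.6 | 38% | 63% |

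**Step 5: precision of the proposed replacement.** For a correlation r between change in QoL and change in HbA1c, the 95% CI is tanh(atanh r ± 1.96/√(n − 3)).

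- n=16, r=0.5: 0.549 ± 1.96/√13 = 0.549 ± 0.544, giving 0.01 to 0.80.
- n=16, r=0.3: −0.23 to 0.69.
- n=23, r=0.5: 0.549 ± 1.96/√20 = 0.549 ± 0.438, giving 0.11 to 0.76. This needs all 23 recruits to complete.

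These intervals describe the replacement analysis. They do not measure the defect in 3.3.

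**The case against.** The strongest reply is that the low carbohydrate diet may mean the diet actually eaten. The food diary records intake daily, with scales and measures supplied, and the records are to be analyzed. Intake differs between people, and QoL could plausibly affect it. This stands as far as it goes. A reader might infer from Step 1 that 3.3 is unanswerable at any sample size because diet has no variance; the documents support that only for the assigned diet. They do not, however, name intake as the diet variable for 3.3, and Table 4 would still have the roles wrong.

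A reader might also infer that no time order exists because QoL and HbA1c are measured at the same two visits. That is not supported. QoL before the intervention, intake during weeks 1 to 12 and HbA1c afterwards form an ordered sequence. The remark about bidirectional associations explains a figure; it is context and not a separate error.

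Next, Table 4 is a brief summary in a condensed article, and stepwise regression can form part of a mediation analysis. The absence of path formulas is therefore no finding. The contradiction in variable roles is one, because it lies in what the table states.

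Finally, the Abstract's primary outcomes do not include mediation, the sample size rests on HbA1c, and phase 3 is a pilot. All true, and 3.1 and 3.2 do not depend on 3.3. But the Outcomes section does label 3.3 primary.

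**Conclusion.** The point holds in this form: the diet as assigned cannot mediate the QoL–HbA1c relationship in a single-group study, and the roles and analyses that Table 4 states for 3.3 cannot produce a mediation result. It affects one of three phase 3 primary outcomes and leaves the other two as they are. The conclusion about the assigned diet follows from the design and needs no numerical assumption.

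Mediation by measured intake remains possible in principle, but the article does not define it. At the planned size it would be very imprecise: power of 3% to 38% at n=16 and 7% to 63% at n=23 across the assumed paths of 0.3 to 0.6.

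**What to change.** - In Outcomes and in the last row of Table 4, remove the word *mediates*. Restate 3.3 as an exploratory, non-primary description of the association between change in QoL and change in HbA1c over 12 weeks, reported as a slope or correlation with a 95% CI.
- Correct the variable roles in that row to match, for example change in QoL as the explanatory variable and change in HbA1c as the response, with no causal reading.
- If a diet variable is to be kept, define it as diary-measured carbohydrate intake and label that analysis exploratory as well.

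The cost is one primary claim given up and two places reworded. Because Outcomes states that there are no secondary outcomes, an exploratory tier has to be added. No visit, measurement or procedure changes. The article reports phase 1 still recruiting and phase 3 planned for February 2021, so on its own timetable the change could be made before phase 3 data exist.

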**Figure 1 figure1:**
[figure not shown]
The association between adults living with type 1 diabetes mellitus, quality of life, and glycemic control. CDE: credentialed diabetes educator; CHO: carbohydrate; PO: primary outcome; T1DM: type 1 diabetes mellitus.

#### Study Phase 1: Australian Diabetes-Specific QoL Questionnaire Development and Piloting

A qualitative approach will be implemented to analyze data collected from audio-recorded participant interviews. Coding will be undertaken using an interview question guide as a framework. The question guide includes the following categories: technical aspects, formatting and layout, participant understanding of the questionnaire aim and purpose, interpretation of the questions, time taken to complete the questionnaire, and any other feedback to improve the usefulness of the questionnaire. In addition, divergence and concordance of participant opinion will be noted. Following this process, data will be cross-checked by a second CDE (trained coder). Any discrepancies will be resolved by a round table discussion with the study team, and questionnaire items to be revised will be determined at this forum.

#### Study Phase 2: Online Australian Diabetes-Specific QoL Questionnaire Validation; and Study Phase 3: The Low Carbohydrate Dietary Intervention

Data will be coded, entered into a password-protected database, checked by JP, and cross-checked by the same CDE (trained coder) from study phase 1. Descriptive statistics will be reported using mean and SD. Study phase 2 (including subphases 2a and 2b) and phase 3 data will be analyzed using R statistical software version 3.6.1 or later (R Foundation for Statistical Computing) [72]. Statistical significance will be set at a *P* value <.05.

### Statistical Plan

Table 4 outlines a brief summary of the study objectives, the independent and dependent variables relating to each objective, and the planned statistical analyses to be conducted.

**Table 4 table4:** Brief statistical plan.

Statistical objectives	Independent variable	Dependent variable	Statistical analysis
To develop and pilot the Australian diabetes-specific quality of life questionnaire	Australian diabetes-specific quality of life questionnaire	N/A^a^	Transcribe, code, and identify common themes in the interview data
To validate the Australian diabetes-specific quality of life questionnaire (study developed)	Australian diabetes-specific quality of life questionnaire	Factorial validation indicators: root mean square error of approximation, comparative fit index, and Tucker-Lewis index	Exploratory factor analysis, confirmatory factor analysis, and structural equation modelling
To examine the association between a low carbohydrate diet and glycemic control	Low carbohydrate diet	Glycemic control	Bivariate: ANOVA^b^ and correlations. Multivariate: hierarchical regression controlling for sociodemographic covariates.
To examine the association between quality of life and a low carbohydrate diet	Low carbohydrate diet	Quality of life	Bivariate: ANOVA and correlations. Multivariate: hierarchical regression controlling for sociodemographic covariates.
To investigate whether a low carbohydrate diet mediates the relationship between quality of life and glycemic control	Low carbohydrate diet	Glycemic control and quality of life	Bivariate: ANOVA and correlations. Multivariate: hierarchical regression controlling for sociodemographic covariates.

^a^N/A: not applicable

^b^ANOVA: analysis of variance

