#### Study Phase 3: The Low Carbohydrate Dietary Intervention

A sample size of 16 has been calculated with a 0.05 significance level and power of 0.8 to detect a significant clinical difference of 1.0% in HbA_1c_. A 1.0% change in HbA_1c_ will be used because dietary changes alone have shown to improve HbA_1c_ by 1.0% [60]. To complete the study, 16 participants are required. To account for a 40% attrition rate [12], 23 participants will be the maximum number recruited.

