### Data Collection

#### Study Phase 1: Online Australian Diabetes-Specific QoL Questionnaire Development and Piloting

Volunteering participants will consent to completing both the online questionnaire and a face-to-face interview. Table 1 outlines each questionnaire section and provides a brief description of what is included. The participants’ pilot questionnaire link will be active for 2 weeks. A courtesy email reminder will be sent to those who have not completed or have partially completed the pilot questionnaire after 7 days. It is anticipated that the questionnaire will take 10-15 minutes. Once the pilot questionnaire is completed, the participant will be contacted via phone to arrange a suitable time for either a face-to-face interview at the study hospital or an online interview. It is estimated that the duration of the interview will be 20-30 minutes. Interviews will be undertaken by JP with the aid of a question guide to ensure a consistent approach is followed. Each interview will be audio-recorded and then transcribed verbatim. Common participant feedback will be documented and then reviewed by the research team. This feedback will be used to modify specific items identified as needing improved clarity and concision or to remove them due to irrelevance. The revised version of the online questionnaire will be used in study phase 2, and subphases 2a and 2b.

**Table 1 table1:** Study phase 1: online Australian diabetes-specific quality of life questionnaire completed by adults with type 1 diabetes mellitus (n=25-30).

Questionnaire section	Brief description of items	Source
Section 1: information sheet^a^	Overview of the study	N/A^b^
Section 2: screening questions^c^	Assessment of study eligibility	N/A
Section 3: consent form^a^	Signed by participant	N/A
Section 4: Australian diabetes-specific quality of life questions^d^	A 28-item questionnaire containing 4 constructs measuring diabetes quality of life using a 10-point Likert scale from “very strongly disagree to “very strongly agree”	Adapted from [48,57]
Section 5**:** sociodemographic covariates	Data collection: gender, age, height, weight, diabetes duration, occupation, level of education, etc	Adapted from [61-63]

^a^Participant information and consent form are to be completed online.

^b^N/A: not applicable.

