### Preintervention Procedure

The preintervention appointment will be conducted by a CDE at the study hospital. The CDE will ensure the participant consent form has been completed before commencing the preintervention appointment. The CDE will discuss the study procedure to ensure the participant understands what is required during all phases of the intervention. The CDE will record the participants’ weight (kg) and height (cm) using a seca 763 electronic measuring station. This information will be recorded on a participant data collection form which will be used pre- and postintervention. An HbA_1c_ test will be conducted using a DCA Vantage Analyzer (Siemens Healthineers). Participants will complete the online Australian diabetes-specific QoL questionnaire using a hospital computer. The CDE will provide each participant with a Dexcom G6 CGMS kit. The kit includes a transmitter, sensors, and a sensor applicator, as provided by Dexcom. Novice CGMS participants will be taught how to use the device. During this appointment, the participant will apply the CGM sensor to their abdominal wall, attach the transmitter, and establish a connection between the transmitter and their own compatible smart device to enable recording and displaying of their glucose levels. Participants glucose levels will then record and display glucose level via the Dexcom G6 application, which the participant will install onto their compatible smart device. The Dexcom G6 CGMS kit will be retained by the participant at the completion of the study. Participants will not use their own personal glucose monitor during the study to test blood glucose levels. However, the participant will use it weekly to test blood ketones. The participant will also be required to use their own blood ketone strips for this test.

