Participants will continue with their usual, daily routine; however, they will commence recording food and fluid consumption in a food diary. Participants will be required to complete the daily food diary 1 week prior to commencing the intervention and for the 12 weeks of the intervention. The participant will email this information to the diabetes dietitian weekly to ensure these records are being maintained, as the information will be used in the final data analysis stage. Participants’ individualized meal plans will be emailed to each participant the day prior to commencing the intervention. Each participant will also be provided with digital kitchen scales and measuring cups and spoons to assist with weighing and measuring foods and fluids to ensure accuracy of quantities consumed. These instruments have been supplied by the GCHHS Study, Education and Research Trust Account (SERTA).

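### Table 4 adjusts the Phase 3 regressions only for sociodemographic variables; where they relate quantities that vary between people, the pre-intervention HbA1c and QoL values should enter first

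*Protocol article*

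**What the plan says.** The Statistical Plan section of the protocol article introduces Table 4 as a short summary. Its three Phase 3 rows each give ANOVA and correlations as the bivariate analysis and "hierarchical regression controlling for sociodemographic covariates" as the multivariate analysis. The independent variable in each row is the low carbohydrate diet. The dependent variables are glycemic control, quality of life, or both, with no time point attached.

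The article itemises sociodemographic covariates only in the questionnaire tables for Phases 1 and 2, as "gender, age, height, weight, diabetes duration, occupation, level of education, etc". It gives no separate list for Phase 3.

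The starting values are collected. The Preintervention Procedure section has HbA1c tested at the visit one week before the diet, and "Participants will complete the online Australian diabetes-specific QoL questionnaire using a hospital computer". Both are measured again afterwards. A food diary is kept from that week to the end of the 12 weeks and sent in weekly, "as the information will be used in the final data analysis stage"; what that use is, the article does not say.

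The abstract describes the Phase 3 primary outcomes as changes in HbA1c and QoL over 12 weeks. The sample size section requires 16 completers.

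**The concern.** A person's HbA1c or QoL score before the diet would normally be the best single predictor of the same measure 12 weeks later. Table 4 fills the adjustment set with other variables and leaves that one out. In a regression across people this has two consequences. Stable differences between people stay in the residual, so the slope is less precise. And if the regressor is itself related to where people started, the slope picks up the starting level and can look like an association with the diet or with QoL.

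Both conditions are plausible here. People with a lower starting HbA1c may also eat less carbohydrate during the study, and the Introduction itself links psychological problems with poorer glycemic control, so QoL and HbA1c may well be related before the diet begins. With 16 completers there is little room for either problem.

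**Working it through.** **The plan's own figure.** "A sample size of 16 has been calculated" at a "0.05 significance level and power of 0.8" to "detect a significant clinical difference of 1.0% in HbA_1c". No SD is given, so 16 cannot be reproduced. A two-sided paired t-test (noncentrality 1.0/SD × √n) returns 16 only if the SD of change is about 1.29 to 1.33 percentage points. This calculation concerns the mean change and is unaffected by the present point. Only n = 16 is carried forward.

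**Where adjustment does nothing.** There are two ways to code the diet variable as Table 4 names it.
- *Diet received.* It equals 1 for all 16 people and is collinear with the intercept. An illustrative design matrix has rank 4 with 5 columns, and rank 5 with 6 columns once the starting value is added. The diet coefficient is inestimable in both.
- *Before versus after.* The coefficient is the mean within-person change. In one set of example data it is -1.022 with no covariate, with age, with the starting value, and with both.

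**Where it matters.** Inputs: n = 16, two-sided 5% test, standardized variables, no true effect. The documents give no correlations, so these are assumed: pre-post correlation r = 0.5, 0.7, 0.8; correlation g = 0.3 or 0.5 between starting HbA1c and recorded intake, or between starting HbA1c and starting QoL. The spurious correlation induced is:
- intake with post-intervention HbA1c: r·g
- intake with change in HbA1c: -g·√((1-r)/2)
- post-intervention QoL with post-intervention HbA1c: r²·g
- change in QoL with change in HbA1c: (1-r)·g/2

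For example, at r = 0.8 and g = 0.5 these are 0.40, -0.16, 0.32 and 0.05. At r = 0.5 and g = 0.5 they are 0.25, -0.25, 0.125 and 0.125.

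Simulated false-positive rates (20,000 runs per setting):

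| g | r | Intake, post values | Intake, change | QoL-HbA1c, post values | QoL-HbA1c, change | Starting value(s) as covariate |
|---|---|---|---|---|---|---|
| 0.3 | 0.5 | 9% | 9% | 6% | 6% | 5% |
| 0.3 | 0.7 | 12% | 7% | 8% | 5% | 5% |
| 0.3 | 0.8 | 14% | 6% | 11% | 5% | 5% |
| 0.5 | 0.5 | 15% | 15% | 7% | 8% | 5% |
| 0.5 | 0.7 | 27% | 11% | 15% | 6% | 5% |
| 0.5 | 0.8 | 34% | 9% | 23% | 5% | 5% |

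Separate runs of the same settings agree within about 2 percentage points; the largest post-value rate came out between 34% and 36%.

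The bias in the intake slope has a simple form: r·g on post values and (r-1)·g on change. At r = 0.6 and g = 0.5 that is 0.6 × 0.5 = +0.30 SD and -0.4 × 0.5 = -0.20 SD; simulation gave +0.304 and -0.200, and 0.002 with the starting value as covariate.

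**Precision.** If intake is unrelated to starting level (g = 0), the standard deviation of the slope is 1/√(n-3) = 1/√13 = 0.277 unadjusted and √(1-r²)/√(n-4) adjusted: 0.866/√12 = 0.250, 0.714/√12 = 0.206 and 0.600/√12 = 0.173. The reductions are about 10%, 26% and 38%. Power for an assumed standardized slope of 0.4 rises from about 0.30 to about 0.35, 0.48 and 0.61. When intake and starting level are related, the precision gain shrinks and can reverse: at g = 0.5 and r = 0.5 the adjusted slope is slightly more variable (0.287 against 0.266). There the benefit is removal of bias.

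**The case against.** The strongest reply is that the vulnerable model is not written in the article. Every participant receives a plan with the same macronutrient split, there is one nonrandomized group, and the independent variable is the diet, not carbohydrate eaten. The abstract frames the outcomes as changes, so starting level is already partly taken into account. Table 4 is a summary, nothing says that starting values are excluded, and a fuller covariate list may stand in a document not shown. All correlations above are assumed.

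Much of this stands. A reader might infer from Table 4 that all the Phase 3 associations will be imprecise and confounded by starting level. The documents do not support that: the one-group mean change is untouched, and under either coding of the diet as named, adjustment leaves the diet coefficient as it was or still inestimable.

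Three things remain.
- Outcome 3.3 concerns the relation between QoL and glycemic control, and both differ between people even on an identical diet. Table 4 lists both as dependent variables, so treating one as a regressor for the other is a reading of the stated objective.
- Correlation and regression on diet are estimable within one group only if diet varies between people, and the diary is the evident source of such variation. This too is an inference.
- Change scores reduce the problem without removing it, and for intake they turn the bias in the opposite direction.

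As for brevity, the article is not silent on covariates. It names an adjustment set for each primary outcome, and the values worth most in these models are not in it.

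**Conclusion.** The point holds in a limited form. Table 4 states a sociodemographic-only adjustment set while the starting HbA1c and QoL values are in hand. For the between-person regressions (the QoL-HbA1c relation in 3.3, and 3.1 and 3.2 if recorded intake is the regressor) this can produce spurious associations and, when intake is unrelated to starting level, lose precision. Under the assumed correlations, false-positive rates on post-intervention values run from about 9% to 35% for intake and 6% to 23% for QoL-HbA1c. On change scores they reach about 15% and 8%. With adjustment they are 5%. These rates depend wholly on the assumed values of r and g; with g = 0 there is no bias, only the precision question.

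The point does not touch the mean pre-post change or the sample size of 16. Nor does it settle how diet is to be represented in a one-group study, which Table 4 must state in any case.

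**What to change.** In Table 4, for the regressions across people:
- enter the pre-intervention value of the dependent variable as the first step: HbA1c where HbA1c is the outcome, the QoL score where QoL is the outcome, and both for 3.3;
- enter any sociodemographic variable only after that;
- state that the diet regressor in these models is carbohydrate intake recorded in the food diary, and keep the mean pre-post change as a separate, unadjusted analysis.

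The cost is a line or two of wording, one degree of freedom (two for 3.3) and no new data. The order of entry matters at this size. If the seven named variables in the questionnaire tables were each entered as a single column, 16 - 1 - 7 = 8 degrees of freedom would remain before the regressor of interest, and fewer if occupation or education needed several columns.
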